## Abstract

**Background:**

Recovery Colleges (RCs) have spread across the globe as a new way of supporting people with mental vulnerabilities in their recovery journey. RCs focus on ‘learning’ rather than ‘curing’ and in that line facilitate a transition from being a passive, dependent patient/client to an active, empowered student learning to live life, despite vulnerabilities. Peer support and co-creation are central in RCs, as peers learn from each other by sharing personal experiences with mental vulnerabilities in an accessible, inspiring and stimulating atmosphere. The implementation of RCs is highly encouraged internationally, and as a result RCs and related self-help initiatives increasingly emerge. However, high-quality research on RCs is scarce and there is a call for thorough investigation of (cost-)effectiveness, mechanisms of action, cross-border fidelity and positioning of RCs. In response, this research project aims to fill these gaps.

**Methods:**

This research project entails (1) a prospective quasi-experimental effectiveness study and economic evaluation, (2) a multifaceted qualitative study to elaborate on the mechanisms of action of RCs for those involved (3) a study to develop a (Dutch) Fidelity Measure of Recovery Colleges, and (4) an organisational case study to describe the positioning of RCs in relation to other mental health care services and community-based initiatives. Following the ideals of co-creation and empowerment in RCs we conduct this research project in co-creation with RC students from Enik Recovery College in Utrecht, the Netherlands.

**Discussion:**

This research project will lead to one of the first longitudinal controlled quantitative evaluations of both cost-effectiveness and effectiveness of RC attendance in a broad sense (beyond attending courses alone). Moreover, we will gather data on a micro level (i.e., impact on RC students), meso level (i.e., organisational fidelity) and macro level (i.e., positioning in the care and support domain), capturing all important perspectives when scrutinizing the impact of complex systems. Finally, we will demonstrate the validity and value of embracing experiential knowledge in science as a complementary source of information, leading to a more profound understanding of what is researched.

**Trial registration:**

The prospective quasi-experimental study has been pre-registered at clinicaltrails.gov (#NCT05620212).

## Background

In the ‘90s, recovery in the context of mental health care has been re-defined as the process of learning how to live a meaningful life despite one’s vulnerabilities [1, 2], moving beyond the narrow-minded definition focusing on reducing clinical symptoms alone [3, 4]. As such, recovery is an active and rich process of gaining and maintaining hope, understanding one’s (dis)abilities, personal autonomy, social identity, meaning and purpose, and getting a positive sense of self. At this time, many mental health care services internationally embrace this definition of recovery as they aim to transform patients from passive, dependent consumers into active producers of care [5].

### Recovery colleges as illumination of changing mental health care

Recently, Recovery Colleges (RCs) emerged as a new way of supporting people with mental vulnerabilities in their recovery process. The first Recovery Education Centers opened in the United States in the ‘90s, after which this innovative approach spread across the globe, with especially strong roots of RCs in the United Kingdom (i.e., UK; [6, 7]). RCs move away from the traditional medical model and adopt an educational model instead, with a focus on ‘learning’ rather than ‘curing’ [8]. In this line, people with mental vulnerabilities are considered active, empowered students in RCs rather than clients^1^. Peer support, co-creation and education are key components of RCs, facilitating an environment where one can learn to deal with their vulnerabilities through sharing experiences and in this way build their own lives from their own strengths [8, 9].

Central to an RC is its curriculum: people can participate in recovery-oriented courses and workshops. Some of these courses are based on existing curricula (e.g., Wellness Recovery Action Planning [WRAP], [10]; Honest, Open, Proud [HOP], [11]; Recovery Is Up to You, [12]), other courses result from co-creation among RC students (e.g., courses about stigma, finding meaning in life). Often RCs facilitate additional opportunities, for example to meet peers in a social meeting place, to work as a volunteer (e.g., in the social meeting place or as co-facilitator of courses) or even to attend a retreat (i.e., a multiple-days overnight stay with a recovery-oriented program). In turn, individuals can be involved in an RC as visitors (i.e., visiting the social meeting place), RC course students (i.e., attending a workshop or training), volunteers, *and* employees. Note that we write ‘and’ instead of ‘or’: individuals can be (and often are) active in multiple ways 2. Although people with mental vulnerabilities are the main target group of RCs, anyone who feels addressed may partake [13].

RCs are deemed promising as attendance has been related to increased well-being, quality of life, achievement of personal recovery goals, and reduced service use and costs [13–15]. In turn, their implementation is highly encouraged (inter)nationally (e.g., [16, 17]). Despite this, an extensive body of high-quality studies investigating RCs is lacking (see e.g., [13, 14]). In response, we here describe the protocol for a multifaceted research project aiming to fill this gap. In the following section we describe our four aims: (1) to investigate the (cost-)effectiveness of RCs, (2) to scrutinize the mechanisms of action of RCs for those involved, (3) to develop a fidelity measure for RCs, and (4) to describe opportunities and risks of RCs as part of the care and support domain.

### Aim one: the (cost-)effectiveness of RCs

High-quality quantitative research on the (cost-)effectiveness of RC attendance is extremely scarce. Although several reviews have been conducted [13–15, 18], the majority of included research did not report empirical data, or were not peer-reviewed [13]. Additionally, empirical studies generally had an uncontrolled (pre-post) design, low sample sizes, and/or unvalidated outcome measures. While there are several partial economic-evaluations investigating costs [19–21], there is a paucity of full economic evaluations of RCs (i.e., investigating costs and effectiveness at once). Hence, there have been repeated recommendations for longitudinal and ideally case-control studies with a higher level of evidence [13, 14].

Empowerment is a surprisingly underassessed outcome measure, while empowering RC students is one of the key principles of the RC model [6, 18]. Notably, initial evidence for increased empowerment after involvement in an RC [22], an RC course [10–12], or other peer-led interventions [23] is promising. To that end, the first aim of this research project is to evaluate the (cost-)effectiveness of RCs, with specific focus on empowerment.

### Aim two: mechanisms of action of RCs

While the body of international research on RCs is still in its infancy, qualitative work is more prevalent than quantitative evaluations [13]. Extant qualitative work provides valuable insights regarding the meaning of RCs (e.g., [24, 25]) and underlying mechanisms of action (e.g., [18, 26]). Combining various sources of information in the form of triangulation is especially fruitful to gain a profound understanding of complex phenomena [27]. To do justice to the complexity of understanding individual recovery processes in a dynamic, interpersonal learning environment as an RC, we therefore believe that it is valuable to conduct research embracing information and observations from multiple perspectives and sources. To that end, the second aim of this research project is to describe what RC attendance means for someone’s recovery journey, and which mechanisms of action give shape to that journey, by means of a multifaceted qualitative study.

### Aim three: the fidelity of RCs

Several authors from the UK have described key principles of the RC model [6, 18, 28, 29], which have been aggregated into the UK RECOLLECT Fidelity Measure by Toney, Knight [8]. However, significant variation exists in the way RCs are given shape, within [30] and outside the UK [31]. To illustrate, in the Netherlands one important deviation from the UK principles regards co-creation. In the UK, RCs are co-created with mental health care professionals [8], while most RCs in the Netherlands are 100% peer-run (Dutch Association of Self-Direction and Recovery [32]). Scrutinizing this different situation in the Netherlands will illuminate possible shared values in RCs across international borders, which strengthens the transformational power of the RC model (see also [33]). In turn, the third aim of this research project is to develop a fidelity measure that highlights core elements of Dutch RCs specifically.

### Aim four: the positioning of RCs

As stated, it is increasingly recognized that adequate health care and support of people with mental vulnerabilities entails more than medically oriented care alone. Importantly, in traditional mental health care services existential and social problems such as meaninglessness and loneliness remain unaddressed, while related existential and social components (i.e., finding back meaning in life and engage in meaningful social relationships) are central to recovery (see for example Johnson [34]). RCs are proposed to be ‘the backbone of the community’, as they fulfil that need for existential and social oriented facilities [17]. Yet achieving a successful collaboration within an adequate integrated care system is complex given the variety and fragmentation of relevant parties involved, not only within the health care domain (e.g., [35]) but also in social services (e.g., [36, 37]). To that end, the final aim of this research project is to scrutinize the collaboration between stakeholders and RCs in the care and support domain.

### Co-research as methodology

To increase the quality of our research, and to operate in line with the philosophy of RCs (i.e., embracing co-creation and empowerment as central elements), this research project is conducted in close collaboration between academic researchers and experiential researchers (i.e., the POP group^3^). The POP group consists of nine experiential researchers at the time of writing, who are visitors, students, volunteers and employees of Enik Recovery College (hereafter ‘Enik’ in short). Enik opened its doors as one of the first Dutch RCs in 2015 in Utrecht, the fourth largest city of the Netherlands, after which numerous similar initiatives followed. Given that Enik is a well-established RC in the Netherlands serving as an example to many others, it is the base site of this research project.

The experiential researchers are involved in every step of the way, from recruitment of participants, study design, data collection and analysis, to writing up and disseminating the results. Including experiential researchers in a research team poses many benefits (e.g., [38–40]): (1) recruiting a more inclusive sample, including participants who may be more difficult to reach otherwise, (2) designing studies to match the participants’ skills and vocabulary (3) designing studies to investigate relevant themes that stem from practice (instead of only from literature and theory), and (4) gaining a more coherent and contextualized understanding of the findings.

## Methods

This research project entails four studies: (1) a prospective effectiveness study including an economic evaluation, (2) a qualitative study, (3) a fidelity study and (4) a positioning study. In this section, the methodology of the four studies is described in accordance with applicable guidelines (effectiveness study, STROBE guidelines, [41]; economic evaluation, CHEERS guidelines, [42]; qualitative studies, SRQR guidelines, [43] and COREQ criteria, [44]).

### Study 1: prospective effectiveness and economic evaluation

The first study focusses on the effectiveness of RCs in terms of recovery-related outcomes (study 1A), and entails an economic evaluation of the cost-effectiveness of RCs (study 1B).

#### Research questions

To evaluate the (cost-)effectiveness of RCs, we pose the following research questions (RQs):

RQ 1: Does attending an RC impact empowerment on the long term, and if so, to what extent?

RQ 2: Does attending an RC impact other recovery related outcomes, such as quality of life, (mental) health, loneliness, satisfaction with treatment and support, and self-stigma on the long term, and if so, to what extent?

RQ 3: What is the cost-effectiveness of RCs?

#### Design

Random allocation to conditions is not feasible, since that would counteract the open-to-all accessibility of RCs. To allow for drawing reliable and valid conclusions, we will adopt a quasi-experimental design where RC students (the experimental group) are compared with members of the Dutch panel of people with severe mental illness (i.e., SMI) (the control group), based on propensity score matching. The Dutch panel of people with SMI (hereafter referred to as ‘the panel’) is a national panel with over 1,500 members who have lived experience with mental vulnerabilities. The target group of this panel is specified as “people (aged ≥ 18) experiencing various SMI” and is expected to be similar to the target group of RCs (for more detailed information on the panel, see de Lange, Michon [45]). RC students receive the same questionnaires as members of the panel (i.e., the control group). All participants (in both the experimental and control group) will fill out a survey every six months, for a two-year period (5 assessments in total). To minimize recall bias (e.g., when determining resource use; [46, 47]) and to determine cumulative quality-adjusted life years, outcomes relevant for the economic evaluation were included in all five waves. Relevant measures to determine the effectiveness of RCs will only be included in t_0_, t_2_ and t_4_ to keep the survey length manageable (every year; see Fig. 1).

**Fig. 1 Fig1:**

Participant timeline of the five wave study design

#### Population

All study participants (both experimental and control group) are people with mental vulnerabilities. RC students will be matched with panel members based on relevant key characteristics through propensity score matching [48].

**Inclusion Criteria.** To be included in the experimental group, people need to be current RC students at the moment of recruitment (in any role, so including volunteers and employees). Moreover, participants need to experience SMI or mental vulnerabilities (both self-reported or diagnosed).

**Exclusion Criteria.** Participants are not eligible if they do not sufficiently master the Dutch language to properly understand and fill out the surveys (even with assistance from the POP group experiential researchers). Specifically for the control group, participants will be excluded from the matching procedure if they are involved in an RC or similar initiatives (i.e., recovery-oriented consumer run organisations) at time of the baseline measurement. If panel members visit one of the included RCs at the time of recruitment, they will be allocated to the experimental group.

#### Procedures

**Recruitment.** The recruitment of participants in this study is two-fold. First and most importantly, participants for the experimental group will be recruited from four RCs in the Netherlands. Enik is the base site of this research project, and we additionally include three other RCs for two reasons: (1) to increase the generalizability and quality of our data and (2) to reach a sample size that is sufficiently large to draw conclusions with a satisfactory certainty. The three additional RCs were selected in collaboration with the co-founder of Enik, and were considered to be well-established and based on a similar philosophy.

RC students will be invited via physical (i.e., posters, flyers) and digital promotion material (i.e., email, newsletter, information page on the RC website, video). Furthermore, facilitators of RC workshops will recruit participants in their groups, and the research team (incl. POP group) will actively recruit participants in the RC’s social meeting place and team meetings. In addition, online and physical information sessions will be hosted to provide information about participation, and assistance with enrolling. When willing to participate, participants receive a digital information letter, provide informed consent and fill out an online application form. Members from the POP group can assist participants in this process if necessary.

Second, as part of regular maintenance of the panel, recruitment for the panel is done via physical and digital promotion materials, which will be distributed among the target population in mental health services’ divisions for people with SMI, and in public (e.g., online advertisements or advertisements in newsletters).

**Between-Group Differences.** RC students are considered similar to the panel’s target population in many ways (e.g., SMI, use of care), yet the most important between-group difference is that those in the experimental group are (or have recently been) actively involved with one of the participating RCs, while members of the panel that are included as controls are not.

**Matching.** To control for potential confounding given the natural (non-randomized) assignment of conditions, we will use propensity score matching and/or exact matching. All participants who have completed at least two waves will be considered for the matching procedure.

Variables that will be used for the matching are gender, age, nationality, level of education and diagnoses (psychotic disorders, mood disorders, anxiety disorders, personality disorders, substance use disorders, neurodevelopmental disorders, eating disorders). If someone does not have an official diagnosis, we will use self-reported diagnosis as a proxy. Although potentially relevant, duration of service use will not be used as matching variable since true baseline data are unavailable; the experimental group may be already active at the RC for a significant amount of time at t_0,_ which may have impacted service use. Each participant from the experimental group will be matched to one or more participants from the control group. Given the large sample size of the control group and the limited number of matching variables, we will likely retrieve multiple good matches per RC partaker, reducing uncertainties and increasing reliability.

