#### Analyses

In our primary (cost-)effectiveness analyses we will adopt an intention-to-treat approach. Since RCs attendance is voluntary, RCs are available-to-all and are increasingly implemented in the Netherlands, we are aware that cross-overs during the study’s timeframe are likely to occur (e.g., individuals who were active RC students at t_0_ but not anymore at t_3_, or vice versa). However, given the pragmatic nature of the study, we will not take cross-overs into account and treat participants according to their original condition. Depending on the number of actual cross-overs we might explore their impact in a sensitivity analysis. Another sensitivity analysis will concern the nature of RC attendance. Given the hybrid nature of RC attendance in the Netherlands (e.g., one can follow courses, visit the social meeting ground, volunteer) we will compare effects of RC attendance in the broad sense with effects of RC attendance for students who participate in courses (more in line with international literature). Potential baseline between-group differences that were not accounted for in the matching procedure will be checked and controlled for if needed. We will adopt single imputation nested in bootstrapping to deal with missing values and skewed data [65]. All analyses will be conducted in SPSS version 29 + and/or R version 4.2+. In the following sections, the specific analyses to examine the effectiveness and economic evaluation of RCs are described separately.

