To determine the cost-effectiveness of RC attendance, incremental cost-effectiveness ratios (ICERs) will be calculated for both the CEA and CUA, following Drummond, Sculpher [73]: ICER = (Costs^RC^ – Costs^control^)/(Effects^RC^ – Effects^control^). These ICERS are representative of average incremental costs associated with one additional unit of the measure of effect. Thus, the ICERs of the CEA represent the incremental costs per significant change in self-reported empowerment, and the ICERs of the CUA refer to incremental costs per QALY gained. Analysis will be done according to the intention-to-treat principle. We will use single imputations nested in non-parametric bootstrapping (N > 2500 bootstrapped samples) combined with seemingly unrelated regression equations [65]. Next, incremental costs, incremental effects and ICERS will be calculated. Sensitivity analyses will be conducted to assess the robustness of the findings, for example by running an analysis from the health care perspective (excl. patient and family costs, informal costs and productivity losses) [73].

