Of course, this research project will likely encounter several challenges. First of all, while RCs aim to facilitate an inclusive environment where individuals with all degrees of vulnerabilities can work on their recovery, it is the question to what extent such variety of individuals are actually reached by the RCs. For example, care providers may hold false beliefs that recovery is less relevant for ‘their patients’ [1], or may be concerned about too high expectations in a ‘college’ [82]. Moreover, regardless of whether the actual RC population is representative of its intended target population, the question remains whether our research sample is, too. To illustrate, one common selection bias in mental health research stems from non-participation of people with relatively more severe difficulties (e.g., [83]). Transferability of our findings to the target population of RCs is in that line yet to be determined and should be carefully considered.

Second, keeping participants engaged within a research project can be challenging, especially when adopting a longitudinal survey design with long in-between periods of non-activity (in our case, 6 months). Longitudinal epidemiological research in the field of psychiatry is posed to be especially prone to significant (selective) attrition rates, reducing statistical power and potentially introducing bias when drop-outs are selective [84]. Therefore, repeatedly communicating the importance of participation and having personal contact with participants when possible will have our special attention during the data collection to minimize attrition rates. We also believe that the multi-faceted mixed-methods approach of this research project makes it more attractive for participants to stay involved, as we provide an opportunity to let their voices be heard beyond surveys alone.

To conclude, the implementation of RCs and similar recovery-oriented practices is booming in attempts to redesign mental health care services so that it becomes a sustainable, affordable, effective and person-centred ecosystem. Thorough high-quality research into whether and how RCs can contribute to recovery and how RCs can be successfully implemented is therefore of great importance.

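### The two-wave rule for matching selects the primary sample on response after t0, which does not fit the stated intention-to-treat approach and does not secure t0 or NEL data

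*Protocol article*

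**What the plan says.** All places are in the Protocol article, Study 1 unless noted.

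- **Procedures, Matching:** "All participants who have completed at least two waves will be considered for the matching procedure". The rule covers both groups. It gives no reason and does not say which waves count.
- **Design:** participants "will fill out a survey every six months, for a two-year period (5 assessments in total"). Economic outcomes are asked at all five waves, but "Relevant measures to determine the effectiveness of RCs will only be included in" t0, t2 and t4.
- **Analyses:** "In our primary (cost-)effectiveness analyses we will adopt an intention-to-treat approach". The only explanation concerns people who start or stop attending: "we will not take cross-overs into account and treat participants according to their original condition". For gaps in the data: "We will adopt single imputation nested in bootstrapping to deal with missing values and skewed data".
- **Analysis study 1A:** the third level of the model is the set formed by an RC participant and the matched controls, so unmatched people are not in it.
- **Analysis study 1B:** "Analysis will be done according to the intention-to-treat principle". The responder outcome compares the NEL at t4 with t0.
- **Sample size:** 125 per group, D = 0.3, correlation 0.6 between subsequent measurements, 30% drop-out at t4, power 82.8%.
- **Discussion:** selective attrition is expected, "reducing statistical power and potentially introducing bias when drop-outs are selective". The matching rule is not mentioned there.

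**The concern.** Membership of the primary sample depends on something that happens during follow-up. A person who returns t0 and then stops is deleted before matching. The imputation cannot bring that person back, because it works only on people already admitted. This is a modified set under an intention-to-treat label.

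The two groups also reach the study by different routes: RC students through the colleges, their facilitators and meeting places, controls through a national survey panel. Equal early non-response for equal reasons cannot be taken for granted. The group-by-time contrast and the ICERs both rest on this set.

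The rule also leaves gaps in the data it admits. It does not require t0, yet controls are screened for RC involvement at baseline, the responder outcome needs a t0 NEL score, and the 24-month QALY curve starts at t0.

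**Working it through.** **1. The plan's own figure.** Inputs from Sample size: 125 per group, D = 0.3, correlation 0.6, 30% drop-out at t4. Assumed: two-sided 0.05, NEL at t0/t2/t4, AR(1) correlation, drop-out 15% at t2 and 30% at t4, one post-baseline group effect, no baseline group term. Generalised least squares gives SE ≈ 0.103, and power = Φ(0.3/SE − 1.96) = 82.84%, against 82.8% stated. This is one plausible reading, since the simulation code is not shown. The same model under compound symmetry gives 89.3%; adding a baseline group term gives 71.8% (AR(1)) or 80.5% (compound symmetry). In the reading that matches, drop-out runs from t0 among all 250.

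**2. What two waves guarantee.** Five waves give 10 possible two-wave patterns:

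| Pattern | Count of 10 |
|---|---|
| Includes t0 | 4 |
| t0 NEL plus a later NEL (t0+t2, t0+t4) | 2 |
| Exactly one NEL value (e.g. t0+t1) | 6 |
| No NEL value (t1+t3) | 1 |

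These are possible patterns, not expected frequencies.

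**3. How many people would be t0-only.** The timing of drop-out is not given, so it is assumed, with no returns after leaving.

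- Linear: 0.30/4 = 7.5%, or 125 × 0.075 ≈ 9 per group.
- Constant hazard: 1 − 0.7^(1/4) = 8.5%, or about 11 per group.
- Extreme (all drop-out before t1): 30%, or 37.5 per group.

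If the 125 must already meet the rule, enrolment per group is 125/0.925 = 135.1 (136), 125/0.915 = 136.7 (137) or 125/0.70 = 178.6 (179). Remaining t4 drop-out among those kept would be 1 − 0.70/0.925 ≈ 24%, about 23%, or 0%, not 30%.

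**4. Bias that the rule creates and the fix removes.** Suppose leaving depends only on the observed t0 score, in the RC group only. Leavers start b SD from stayers, and the t0–t4 correlation is ρ. Dropping them shifts the mean change by share × b × (1 − ρ).

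- Share 15%, b = 0.3, ρ = 0.6² = 0.36: 0.15 × 0.3 × 0.64 = 0.029 SD.
- Same, ρ = 0.6: 0.15 × 0.3 × 0.40 = 0.018 SD.
- Share 7.5%, ρ = 0.36: 0.075 × 0.3 × 0.64 = 0.014 SD.

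The share and b are assumptions. If leavers start lower, the rule makes RC change look smaller; if they start higher, larger.

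**5. Bias that the fix does not remove.** Suppose leavers' unseen change is g SD worse than stayers' for reasons not visible at t0. Under the rule the contrast is off by (share in RC − share in controls) × g.

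- 7.5% in both groups: 0.
- 15% vs 5%, g = 0.2 to 0.5: 0.02 to 0.05 SD.
- 30% vs 10%, g = 0.2 to 0.5: 0.04 to 0.10 SD.

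Now take 15% in RC only and g = 0.5. With the rule: 0.15 × 0.5 = 0.075 SD. With everyone matched and equal baselines, the model fills leavers' change from stayers, so the bias is again 0.075 SD. If leavers also start 0.3 SD lower (ρ = 0.36), the model credits them with 0.3 × 0.64 = 0.192 SD more change than stayers, and the bias is 0.15 × (0.5 + 0.192) = 0.104 SD.

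**The case against.** There are five serious points on the other side.

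- **The label.** The article explains intention-to-treat only as ignoring cross-overs and keeping the original condition, and there is no randomised set to break. In that narrow sense the principle can be applied within the matched set. This stands: the rule does not make intention-to-treat impossible. What it produces is a modified set that is not named as one.
- **Direction and size.** A reader might infer that early leavers are RC students doing badly, so that the rule favours RC attendance by up to a third of D = 0.3. The documents do not support this. The same rule applies to both groups, the RC group includes volunteers and employees and people who may have been active for a long time at t0, and panel recruitment continues as part of maintenance. The upper figures in step 5 need early loss well above 7.5% to 8.5%, and they describe non-ignorable drop-out, which exists with or without the rule.
- **Purpose.** The article gives no purpose for the rule. Economic outcomes are asked at every wave, so t0+t1 does yield cost and utility data. It therefore cannot be said that the rule misses its aim, only that it does not secure the primary outcome.
- **Timing.** Matching after follow-up has begun is a minor issue, since the listed matching variables are demographic and diagnostic and none is an outcome.
- **Missing detail.** Analysis sets are often defined in a fuller document. But this rule is stated, and following it as written selects on follow-up. It is not an omission.

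**Conclusion.** The point holds as a conflict between a stated rule and a twice-stated principle. Entry to the primary sample depends on response after t0, t0-only participants lose their usable baseline data before the planned model and imputation begin, and neither t0 nor any NEL value is guaranteed.

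Under 30% drop-out at t4 with linear or constant-hazard attrition, about 7.5% to 8.5% are affected (roughly 9 to 11 of 125 per group). The resulting bias cannot be derived from the document in size or sign; it is zero if exclusions and the outcomes of those excluded are alike in both groups. The part that belongs to the rule itself is about 0.03 SD under the illustrative 15% loss and 0.3 SD baseline gap, and about half that at 7.5%. The larger values, up to 0.10 SD, should not be charged to the rule, because the change below would leave them in place. Nor does the check show that 82.8% power is wrong; it shows only that the article does not say whether the 125 per group are counted before or after the two-wave rule.

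**What to change.** Replace the sentence in Matching with:

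> *All participants with a completed t0 survey are considered for matching, irrespective of later response; matching uses t0 data only and is fixed before follow-up outcomes are examined.*

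Then:

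- handle later missing waves with the mixed model and imputation already planned;
- report the number and t0 characteristics of t0-only participants by group;
- keep the two-wave set as a sensitivity analysis, so that the influence of the rule can be seen;
- add a separate sensitivity analysis for non-ignorable drop-out, which the new sentence does not address.

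No new data are needed. The cost is more values to impute and one further sensitivity analysis. If the 125 per group are counted at t0, the stated sample size and drop-out assumption stay as they are.
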